### Participant timeline

Details of the study timeline and flow of participant are shown in Figs. 1 and 2.

**Fig. 1 Fig1:**
[figure not shown]
Study timeline

**Fig. 2 Fig2:**
[figure not shown]
Flow of participant

Meanwhile, the overall arrangement of trial timeline is as follows:

2020.1-2022.12: Design, program demonstration, preliminary preparation and pilot study.

2023.2-2024.12: Conduct the formal national multicenter study.

### Sample size and groups

In the present study, the sample size is determined primarily by the following factors: [1] It is difficult to maintain the compliance of the community population, which necessitates a significant investment of workforce by the research team to maintain compliance; [2] The quality control difficulty of multidomain intervention is high, and more human and material resources required in supervising the quality of each link of the research; [3] Screening of potential subjects in the community requires high time and cost; [4] Due to the reasons of research content and funding, the number of our team members is limited; [5] MCI prevalence was set as P = 0.34 [25], power = 0.95, and dropout rate = 0.2. Therefore, considering scientific and practical feasibility and other factors, according to the sample size calculation method of RCT study [26], the total sample size of the single center would be 90, with 30 participants in each community. We have given the basis for calculating the sample size of a single sub-center. However, because China has a large geographical area, each region may have different characteristics. Therefore, in the study design, we calculated the sample size required by only one sub-center, in order to balance the influence of different regional bias factors on the overall effect of the study by adding sub-centers in different regions into the overall study, so as to evaluate the effect of multi-domain intervention more objectively. Therefore, this study intends to include 12 sub-centers to participate, with a total sample size of 1080.

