Mild cognitive impairment (MCI) is an intermediate stage between normal aging and dementia. The latest evidence reveals that the prevalence of MCI among older adults aged 60–64 years has increased from 6.7 to 25.2% among older adults aged 80–84 [6]. However, the average prevalence of MCI in China is approximately 20.8% [7]. After three years, up to 44% of MCI patients can be converted into AD, which is ten times higher than the general population, and the probability of developing AD within five years is as high as 70%, which is the main factor for the occurrence of AD [3]. Therefore, there is a “time window” for intervention to delay disease progression and treatment. Existing evidence indicates that intervention at this stage can effectively slow or prevent MCI from progressing to dementia [8], which significantly impacts promoting healthy aging in China.

At present, some research evidence suggests that single intervention such as exercise, nutrition, sleep and meditation had a positive effect on promoting cognitive function.

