Non-contact control group [1]. whether to prepare small gifts for participants during traditional Chinese festivals; [2] The number of subjects in this group should be increased appropriately (by about 10%) to cope with the dropout due to uncontrollable factors.

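### The 0.95 power is stated for one sub-centre and rests on an MCI prevalence that is not a trial outcome; it is invalid at that level, and the power of the 36-community trial is not established

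*Protocol article*

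**What the plan says.** The section on sample size and groups (protocol article) lists five determinants of the sample size. Four are practical: compliance, quality control, screening cost and team size. The fifth is statistical: "MCI prevalence was set as P = 0.34 [25], power = 0.95, and dropout rate = 0.2". Citing a published method for RCTs, the section concludes that "the total sample size of the single center would be 90, with 30 participants in each community". It is explicit about the level of the calculation: "in the study design, we calculated the sample size required by only one sub-center". Twelve sub-centres are then included to balance regional differences, which gives 1080.

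Four other sections bear on this:
- **Inclusion criteria:** a baseline MoCA below 26 is required, so cognitive impairment is a condition of entry.
- **Primary outcomes:** a set of cognitive scales, and MRI measures.
- **Trial design and study setting; Sequence generation:** three communities per sub-centre, one per arm, with the intervention allocated to the community as a whole. The second random step picks residents within a community and does not allocate them to arms.
- **Groups perform standards and quality control:** the non-contact group is to be enlarged by about 10% to cover dropout.

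**The concern.** A power figure needs an outcome, a difference in that outcome, and the level at which arms are compared. The prevalence of MCI supplies none of these. Among people already selected for impairment it can describe how many residents must be screened, but not how arms will differ on a cognitive score.

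The level is a second difficulty. In one sub-centre each arm is a single community, so any difference between two arms is also a difference between two communities, and nothing in that sub-centre's data separates the two.

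This is the only power statement in the article. If it stands, a null result, or a contrast from one sub-centre, could be read as coming from a comparison with 95% power.

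**Working it through.** **Inputs from the protocol article.** P = 0.34, power 0.95, dropout 0.2, 30 per community, one community per arm per sub-centre, 12 sub-centres.

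**Assumptions (not in the article).** Two-sided 5%; ICC 0.01, 0.02 and 0.05; no credit for baseline adjustment or for blocking by sub-centre.

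**1. The plan's own figures.** 3 × 30 = 90 and 12 × 90 = 1080, so the multiplication is right. Evaluable per community: 30 × (1 − 0.2) = 24. Evaluable per arm over the trial: 12 × 24 = 288.

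**2. Does 30 per arm at power 0.95 follow from P = 0.34?** Not without a second value. Treating 0.34 as one of two proportions and inflating for dropout, 30 per arm results if the other proportion is:
- about 0.82 to 0.83 (two-sided);
- about 0.85 to 0.86 (two-sided with continuity correction);
- about 0.78 to 0.79 (one-sided);
- 0 (one-sided), a degenerate case.

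The article states none of these, and a proportion with MCI is not an outcome of the trial in any case.

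**3. One sub-centre, valid analysis.** With one community per arm, the degrees of freedom for between-community variation within arms are 1 − 1 = 0 in each arm. No test of arm against community variation can be formed, whatever the effect size.

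**4. One sub-centre, clustering ignored.** For a two-sample t-test with 24 per arm, 95% power requires a difference of 1.06 SD. (The normal approximation gives (1.960 + 1.645) × √(2/24) = 1.04 SD.) Power is 17% at 0.3 SD and 40% at 0.5 SD.

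Such a test would also not hold its error rate. With design effect DE = 1 + (24 − 1) × ICC, the true level of a nominal 5% test is about 2 × [1 − Φ(1.96/√DE)]: 7.7%, 10.5% and 18.1% at ICC 0.01, 0.02 and 0.05.

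**5. Whole trial, two arms compared.** With 12 communities per arm, df = 2 × (12 − 1) = 22. The detectable difference in SD units is

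d = (t₀.₉₇₅,₂₂ + t_power,₂₂) × √(2 × DE / 288),

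where t₀.₉₇₅,₂₂ = 2.074, t₀.₉₅,₂₂ = 1.717 and t₀.₈₀,₂₂ = 0.858.

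| Assumed ICC | DE | √(2·DE/288) | d at 95% power | d at 80% power |
|---|---|---|---|---|
| 0.01 | 1.23 | 0.0924 | 0.35 | 0.27 |
| 0.02 | 1.46 | 0.1007 | 0.38 | 0.30 |
| 0.05 | 2.15 | 0.1222 | 0.46 | 0.36 |

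**6. Enrolment total.** If the extra 10% in the non-contact group applies at every centre, that community becomes 33, and 12 × (33 + 30 + 30) = 1116, against 1080 stated.

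**The case against.** A reader might infer that the trial as designed lacks 95% power. The documents do not support that. Power is undefined until a target difference is named, and by the table above 36 communities could reach 95% for moderate effects.

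It is also an inference that 90 came from the prevalence alone, since the section weighs it together with four feasibility limits and cites a method that is not reproduced. The article condenses a fuller protocol, so the absence of an effect size, alpha, SD or ICC is not counted here as a fault. What stands is the input and the level that the article does state: a prevalence offered as the basis for power, and a calculation declared to be for one sub-centre.

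It can fairly be said that no between-arm test within one sub-centre is planned, and that the analysis aims at the overall effect. That makes a misleading sub-centre result less likely. It does not help the power figure, which is then attached to a comparison that nobody will make, while the comparison that will be made has none.

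The illustrative differences are on the cautious side. The planned model adjusts for the baseline response, and sub-centre acts as a block. With an assumed baseline correlation of 0.7 acting at both levels, 0.38 SD would shrink to 0.38 × √(1 − 0.7²) = 0.27 SD. The ICCs are assumptions too.

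The 10% enlargement reads as a practical contingency. The gap of 36 participants is 36/1080 = 3.3%, an editorial matter that does not bear on the power argument.

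**Conclusion.** The concern holds in a limited form. The 0.95 is unsupported by its stated inputs and invalid at the level for which it is stated, because a sub-centre with one community per arm allows no valid between-arm test. The total of 1080 inherits no power from it. Power for the 36-community trial is not established, which is different from being shown to fall below 0.95.

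The sub-centre conclusion follows from the design alone and needs no assumed value. The sizes do depend on assumptions: two-sided 5%, 24 evaluable per community, the ICC range, and no credit for baseline adjustment or blocking. On those, the existing sample detects roughly 0.35 to 0.46 SD at 95% power, or 0.27 to 0.36 SD at 80%. As this is the article's only power statement, it should be corrected before results are interpreted against it.

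**What to change.** Rewrite the sample-size paragraph as follows.

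1. Withdraw the prevalence-based power of 0.95 for a single sub-centre. If 0.34 is kept, describe it as an expected screening yield.
2. State what the existing sample can detect at trial level: 12 communities per arm, 30 enrolled and 24 evaluable in each, as a detectable difference on one listed primary cognitive score chosen by the sponsor (for example MoCA at 6 months), over a stated ICC range. If baseline adjustment is credited, show the assumed correlation.
3. State that comparisons within a single sub-centre are descriptive.
4. As a minor point, reconcile 30 per community and 1080 with the roughly 10% increase in the non-contact group, which gives 1116 if applied at every centre.

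The cost is one rewritten paragraph and a less favourable stated figure. No participants are added, and the allocation and procedures do not change.

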### Recruitment and screening

Considering the difficulty and high dropout rate of community intervention studies, this study split all assessment/examination content of subjects into 4 steps, recruited a sufficient number of potential subjects at one time to enter the step 1, and then assessed participants’ compliance through repeated assessments of participants (steps 2 to 4, with 2–5 days intervals between each step). Finally, subjects with strong enough adherence are screened for formal study. The following are the main 4 steps in the participant screening process:

The research team disseminates the program in the community and compiles a list of potential participants by encouraging community residents to sign up.Potential participants who meet the eligibility criteria will participate in a preliminary screening for the risk of cognitive impairment (with a sample size of more than 100 people in each community). The assessment content will mainly focus on a special assessment of cognitive domains. This assessment time will be approximately 30–40 min for each person. Participants who complete this step are considered to have passed the first compliance test.A team of doctors is organized to provide community on-site answers to the preliminary screening results in the community. The potential participants are invited to participate in the cognitively related risk factors (such as the ability to live daily, anxiety, and depression). Subjects who successfully completed this step have passed the second compliance assessment.The community research manager will call the potential participants (after two rounds of compliance assessment), invite them to take part in biological sample testing and functional MRI under the condition of obtaining their consent and signing the ethical, informed consent, and finally determine the list of participants.

The recruitment standardization of each participant must go through three rounds of quality control work before he or she formally enters the study:

The data platform manager screened out the list of eligible participants based on the assessment results recorded in the database and submitted it to the PI for the second round of review;The principal investigator (PI) reviewed the eligibility conditions of the participants in the list again based on eligibility criteria and submitted the list to the community manager for the third round of confirmation;Community managers conducted community on-site interviews with the community participants, informed them about the content of the informed consent again, and signed the informed consent will be by the participants themselves.

### Interventions

Our study will be mainly composed of Multidimensional intervention group, Health education intervention group and non-contact control group. The implementation scenarios of all research processes (except MRI) under this research project will be completed in the community. Each study group receives varying levels of cognitive health risk factor intervention, as presented in Table 1.

**Table 1 Tab1:** Interventions and groups setting

Section	Non-contact control group	Health Education Intervention	Multidimensional Intervention
Exercise intervention	**×**	**×**	**√**
Sleep intervention	**×**	**×**	**√**
Meditation intervention	**×**	**×**	**√**
Dietary intervention	**×**	**×**	**√**
Health education intervention	**×**	**√**	**√**

#### Multidomain intervention group

According to the study design, the intervention methods in the present study primarily included exercise training, sleep guidance, meditation training, dietary guidance, and health education. Each community will provide an activity room (about 100 square meters) for our project, and all interventions will be implemented in the community where the subjects live.

In the exercise intervention part, the project team invited geriatrics and physical training experts to develop a six-month advanced exercise training program tailored to the physical characteristics of older adults in China. Resistance training, aerobic exercise, flexibility & balance training, and traditional Chinese exercise were the main components of the exercise program (modified Taijiquan and Baduanjin) (Table 2). Two fixed physical training experts guided all subjects in the multidimensional intervention group through the entire exercise intervention process. The intervention method is offline group intervention with an intervention frequency of three times per week, and each intervention lasts approximately one hour. The following is the main process of exercise intervention (Table 3): [1] pre-exercise mobilization, the coach introduces the course content, understands the status of the subjects, and encourages the subjects to exercise; [2] warm-up exercise, primarily static stretch; [3] formal training courses shall be conducted following the established training plan; [4] relaxation exercise, primarily static stretch; [5] post-exercise stimulation, the coach summarized the training situation, subjects provided feedback on training feelings and questions, and the coach gave positive stimulation and introduced the general content of the next training course.

**Table 2 Tab2:** Subject’s advanced training intensity level and arrangement (6 months)

Training action package intensity levels	Month					
	Level 1 (L)		Level 2 (M)		Level 3 (H)	
	1	2	3	4	5	6
★ (L)	**√**	**√**				
★ ★		**√**	**√**	**√**		
★ ★ ★				**√**	**√**	
★ ★ ★ ★					**√**	**√**
★ ★ ★ ★ ★ (H)						**√**

Note: Each training package includes Resistance training, aerobic exercise, flexibility & balance training, and traditional Chinese exercise, etc. With the increase of stars, the training intensity is also gradually increasing

**Table 3 Tab3:** The main process and content of exercise intervention course

Contents	Step 1	Step 2	Step 3	Step 4	Step 5
	Pre-exercise	Warm-up	Formal training	Relaxation exercise	Post-exercise
Mobilization	**√**				
Static stretch		**√**		**√**	
Training package			**√**		
Summary & feedback					**√**

The sleep intervention section mainly relies on community on-site sleep guidance to carry out the intervention. The target participants receive sleep assessment, Q&A, healthy sleep behavior guidance, and feedback. This is the responsibility of the sleep expert, and offline, sleep guidance will be conducted every 1.5 months.

Meditation intervention, with the same frequency as exercise intervention (three times per week). Meditation experts train participants for 15–20 min after each exercise intervention. The meditation expert guided the group members to give feedback and answer questions about the effect of meditation at the end of each complete intervention and pushed the participants to communicate their feelings about meditation.

In the dietary intervention section, according to the characteristics of energy intake/consumption of the older adults in China, and with reference to the “Mediterranean diet” to formulate strategies, nutrition experts are invited to formulate grading factors with “energy level” as the dietary recommendation principle. In each “energy level”, a different diet is assigned, with the goal of “promoting cognitive health” as the overarching goal. The nutrition experts matched specific recipes for the subjects and interpreted them one-to-one based on the participants’ diet scale and diet-related behavior assessment results. Every 1.5 months, nutritional dietary counseling will be provided. Simultaneously, after each offline exercise and meditation intervention, the participants are urged and reminded to eat according to their diet and given positive incentives.

#### Health education intervention group

Community on-site group teaching are used for the health education part of the present study, which covered 24 learning topics (Frequency & form: 1 h each time, once a week for 6 months, fixed time and place) such as scientific exercise, joint pain, healthy sleep, nutritious diet, hypertension, diabetes, cognitive disorders, diseases, and new therapies for older adults. The project team will prepare the paper publicity materials based on the theme of each lecture and distribute the health education materials before each lecture. More than ten doctors were organized to conduct a six-month offline health education intervention course for the target participants in the pilot trial of our study.

#### Non-contact control group

Subjects in this group only performed compliance related maintenance work, such as birthday greeting messages and holiday gifts (such as a bouquet of flowers), in addition to enrollment and exit assessment.

During the implementation of this study, when the subjects feel that the experimental intervention has a high risk to themselves or increases the burden of disease, our team will fully communicate with the participants and give professional advice. If the subjects still insist on withdrawing after full consideration, the research team will respect the requirements of the subjects and make relevant records.

### Assignment of interventions

#### Sequence generation

The randomization of the code is shared by the data platform manager and PI. Whole random process of this study mainly consists of two steps. The first step is to carry out the random assignment work with the community as the basic unit, select 3 communities at random within the main urban area of the city where the sub-center is located, and use the computer generator randomizer method to determine the intervention content of each community. The second step of the random process is to carry out random assignment with individual residents as the basic unit, and the computer generator randomizer method is used to randomly screen all the candidate subjects in each community who have completed all assessments and are willing to participate in this study, finally the final list of subjects in each community is randomly confirmed. The PI will collect the participants’ cell phone number list and community list, and the data platform manager will use the computer generator randomizer method to match each cell phone number with a random code. The PI then distributes the community and participant codes to the community managers, who use them to carry out the sequence generation.

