**Methods:**

Our study was designed as a national multicenter, community-based randomized controlled trial (RCT). Twelve medical institutions in ten Chinese cities will participate in our study from 2020 to 2024, and 1080 community residents aged 50 and above will be enrolled as participants. Each sub-center will be responsible for 90 participants (30 people per community) across three communities (non-contact control group, health education group, and multidomain intervention group). The community will be the basic unit of the present study, and all participants in each community will receive the same intervention/control measure. Three working groups are set up in each sub-center to manage the three communities independently to minimize interference at the implementation level between the groups. The multidomain intervention group will receive integrated interventions including exercise, nutrition, sleep, health education and mindfulness meditation. All data generated by the research will be analyzed and processed by statistical software (such as SPSS 21.0, Python 3.0, etc.), and part of the research data will be displayed in the form of graphs and tables.

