#### Randomization, allocation and concealment

The roles involved in the implementation of the study in each sub-center included PI, data platform manager, participant, community manager (research team), community partner, multidimensional intervention implementation team, health education implementation team, cognitive assessment team, and radiology testing team. A computer generator randomizer method (PI execution) is used to determine the intervention content in each community, and PI is responsible for conducting specific research work in each sub-center. This study could not achieve a perfect “blinding” because the participants are able to clearly perceive the intervention, but we tried to maximize the “isolation” of the intervention/control implementation team in each group to reduce the interaction between the groups.

The intervention/control settings of the three communities in each sub-center are assigned by the platform manager using the computer generator randomizer method to achieve the randomization process in our study.

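### Communities are allocated to arms before residents are recruited and nothing conceals the arm from recruiters, so who enters the study may differ by arm

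*Protocol article*

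**What the plan says.** All references are to the protocol article.

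- **Unit.** The abstract's Methods make the community the unit: "all participants in each community will receive the same intervention/control measure".
- **Order.** Sequence generation describes two steps. "The first step is to carry out the random assignment work with the community as the basic unit": three communities are picked in the sub-center's city, and staff "use the computer generator randomizer method to determine the intervention content of each community". In the second step the computer is used to "randomly screen all the candidate subjects in each community who have completed all assessments and are willing to participate in this study".
- **Who allocates.** Sequence generation says that the PI and the data platform manager share the randomisation code. Randomization, allocation and concealment first states: "A computer generator randomizer method (PI execution) is used to determine the intervention content in each community". Later in the same section the settings of the three communities "are assigned by the platform manager using the computer generator randomizer method".
- **Who decides entry.** Recruitment and screening has four assessment steps, with compliance judged along the way and only those who adhere well enough going forward. The community research manager telephones candidates for the last step. Three review rounds follow. The data platform manager screens the list, the PI "reviewed the eligibility conditions of the participants in the list again based on eligibility criteria", and the community managers interview residents on site and obtain consent.
- **Concealment.** The section with that word in its heading concedes that blinding is imperfect and describes keeping the teams apart. It does not say that the arm is hidden from those who recruit or from those who sign up.

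**The concern.** When whole communities are randomised, chance decides which communities get which arm. It does not decide which residents of those communities enter the trial. If residents are found and consented after the arm is fixed, and someone in that process knows it, entry can depend on the arm. This is identification (recruitment) bias.

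Here the offers differ sharply. The multidomain arm is asked to attend exercise and meditation three times a week for six months, the education arm a weekly lecture, and the control arm only the enrollment and exit assessments plus greetings and gifts. Willingness to sign up, return for repeated assessments and consent could reasonably differ between these. The arms could then differ in motivation, health or expected cognitive change before any intervention starts. Enrolling more people per community would not remove such a difference.

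**Working it through.** **1. Order of events.** Screening can take place only in communities already picked. Picking and allocating are one step in Sequence generation. On the text as written, therefore, the arm exists before sign-up, the four screening steps, the review rounds, consent and the draw. No section says that residents are identified or consented before allocation.

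**2. Roles side by side.**

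| Role | Part in allocation | Part in entry |
|---|---|---|
| PI | Shares the code; named as running the community allocation | Eligibility round two |
| Data platform manager | Shares the code; also named as assigning the communities | Eligibility round one; does no community work |
| Community manager | None stated; is tied to one community, hence one arm | Calls candidates; final interview and consent |

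Whichever of the two statements on the allocator is right, that role also reviews eligibility.

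**3. What the computer draw does.** It is made within each community, among candidates who are assessed and willing. A random sample of a pool has the same expected make-up as the pool. If the three pools differ because of how they formed, the three final lists differ in the same way.

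**4. Size, as an illustration.** The article gives no figure for this bias, so there is none to reproduce.

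- From the article: 12 sub-centers with one community per arm each, so 12 communities per arm; 30 participants per community; 20% dropout. Completers per community: m = 30 × 0.8 = 24.
- Assumed: ICC of 0.01 to 0.05; outcome in SD units; two-sided 5% test of two arms on 12 + 12 − 2 = 22 df; selection shift between arms of 0.1 to 0.2 SD.

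SE = √[ 2/(12m) × (1 + (m − 1) × ICC) ]

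- ICC 0.01: √[ 2/288 × 1.23 ] = 0.0924
- ICC 0.05: √[ 2/288 × 2.15 ] = 0.1222

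The noncentral t on 22 df needs a noncentrality of 3.774 for 95% power.

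- ICC 0.01: 3.774 × 0.0924 = 0.349 SD
- ICC 0.05: 3.774 × 0.1222 = 0.461 SD

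Shift as a share of the detectable difference:

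- smallest: 0.1 / 0.461 = 22%
- largest: 0.2 / 0.349 = 57%

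With no true effect, the chance of a significant result is P(|Z + b/SE| > 1.96) for a shift b, by normal approximation and without covariate adjustment. It is 13–19% at b = 0.1 and 37–58% at b = 0.2, against a nominal 5%.

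**The case against.** Much of the case on the other side is sound and limits what may be claimed.

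- **Staff do not hand-pick participants.** A reader might infer this from the overlap of roles. The final list is a computer draw, and the PI's round checks against written criteria. Staff shape and review the pool; they do not choose the final 30.
- **Knowledge of the arm at sign-up is inferred.** The article does not say what residents or community managers are told, or when. Sequence generation also ends with coded lists passing to community managers who then carry out sequence generation, which could be read as a later step. That is ambiguous and does not undo the stated first step.
- **The larger control list proves less than it seems to.** Groups perform standards and quality control asks for about 10% more control participants, to cover dropout. That shows the arm is known when list size is set, which could be as late as the draw. Unequal list size does not itself bias the comparison, so removing it is a matter of preference.
- **Going from more than 100 screened to 30 enrolled does not measure discretionary selection.** Part of the reduction is common eligibility criteria and part is the random draw. The number left before the draw is not given.
- **Controls are not offered nothing.** They receive the screening feedback from doctors, the enrollment and exit testing, and gifts.
- **Randomisation is not lost.** Community-level features are still balanced in expectation, and the Statistical methods plan to adjust for baseline response and other covariates as needed.

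None of this supplies concealment. Separate teams limit contamination between arms but leave each community manager serving a single arm. Covariate adjustment cannot reach unmeasured motivation or expected change.

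**Conclusion.** The concern holds as a weakness in the design. Followed as written, the plan allocates communities first and recruits residents second, with no stated concealment and with the allocating roles also reviewing eligibility. The comparison is therefore open to identification bias, of unknown direction and unknown size. The article does not show that such bias has occurred or that anyone recruits with the arm in view. It also does not support the claim that randomisation no longer protects the comparison at all.

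The range of 22–57% of the detectable difference shows only that a modest shift would matter. It rests on the assumed ICC, the assumed shift of 0.1–0.2 SD, which has no basis in the article, 24 completers in each of 12 communities per arm, and a t-test on 22 df. Separately, the two statements on who allocates the communities contradict each other and must be reconciled.

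**What to change.** **Sub-centers not yet allocated.** In all three communities, complete recruitment, the four screening steps, baseline assessment, consent (worded for all three possible arms) and the random draw. Lock the three lists on the platform. Only then allocate the communities, by one named role outside community recruitment: the data platform manager, not the PI. That role also runs eligibility round one, which does no harm once the lists are locked before allocation. In Randomization, allocation and concealment, delete the parenthesis giving execution to the PI, so that one allocator is named throughout.

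**Sub-centers already allocated.** As far as possible, withhold the arm from residents, from community managers and from the PI as eligibility reviewer until the list is locked. Report the order of recruitment and allocation in these sub-centers as a limitation.

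The article schedules the formal study from February 2023. It reports that by May 2023 eight of the 12 sub-centers had completed ethics applications and agreements, leaving four. It does not say which had allocated communities, so the sponsor should establish this first.

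**Cost.** A protocol amendment and coordination, with no added sample size. The three communities of a sub-center must finish screening together, and activity rooms must be agreed before the arm is known. Where allocation has already taken place, the change can only reduce the problem.
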